## Abstract

**Background:**

Autosomal dominant polycystic kidney disease (ADPKD) is considered the most common inherited renal disease. Patient-Reported Outcomes (PROs) and patient experience in ADPKD are difficult to quantify and have not been well studied, particularly in the early stages of the disease. There is evidence to suggest that early-stage ADPKD patients have a lower Health-Related Quality of Life (HRQoL) than the general population due to the signs and symptoms of early-stage ADPKD. However, no research has been carried out on the HRQoL of early-stage ADPKD patients using validated ADPKD-specific PRO measures. Additionally, a new disease progression delaying treatment option has recently emerged for ADPKD. Patient preference for this treatment and unmet treatment needs have not yet been investigated.

**Methods:**

The ACQUIRE study is a prospective, observational study investigating the influence of early-stage ADPKD-related symptoms and treatments on PROs. It aims to collect real-world data on patient demographics, treatment patterns, clinical outcomes, and PROs such as HRQoL, treatment satisfaction and treatment preference in early-stage ADPKD. Adult ADPKD patients in stages 1–3 of chronic kidney disease (CKD) with evidence of rapidly progressing disease are being recruited from seven European countries. At baseline and every 3 months, for a follow-up period of 18 months, general and disease-specific questionnaires are completed remotely to capture patients’ own assessment of their overall and ADPKD-related HRQoL. A Discrete Choice Experiment (DCE) is also used to investigate the value patients place on different attributes of hypothetical treatment options (e.g. treatment outcomes, side effects) and the role each attribute plays in determining overall patient treatment preference.

**Discussion:**

The results of this study will highlight the real-world effects of ADPKD-related challenges on PROs including HRQoL, treatment experience and satisfaction; and help physicians gain greater insight into likely disease outcomes based on early-stage patient symptoms and patients’ experience with treatment. Data captured by the DCE may inform ADPKD treatment decision-making from a patient perspective. The DCE will also provide insights into which patients are more likely to perceive benefit from treatments based on the value and trade-offs they place on specific treatment attributes.

**Trial registration:**

NCT02848521.

**Protocol Number/Version**: 156–303-00096/Final

**World Health Organization Trial Registration Data Set**

**Table Taba:** 

Data category	Information
Primary registry and trial identifying number	ClinicalTrials.gov
Date of registration in primary registry	July 21, 2016
Secondary identifying numbers	156–303-00096
Source(s) of monetary or material support	Otsuka Pharmaceutical Europe Ltd
Primary sponsor	Otsuka Pharmaceutical Europe Ltd
Secondary sponsor(s)	N/A
Contact for public queries	Study Director, Medical Department Otsuka EuropeTel: [name]
Contact for scientific queries	Study Director, Medical Department Otsuka EuropeTel: [name]
Public title	A Study Measuring Quality of Life, Treatment Preference and Satisfaction of ADPKD Patients in Europe
Scientific title	A Prospective, Non-interventional Study Measuring Quality of Life, Treatment Preference and Treatment Satisfaction of Autosomal Dominant Polycystic Kidney Disease Patients in Europe
Countries of recruitment	Austria, Belgium, France, Germany, Spain, Switzerland, United Kingdom
Health condition(s) or problem(s) studied	Autosomal Dominant Polycystic Kidney Disease
Intervention(s)	N/A – this is a non-interventional study
Key inclusion and exclusion criteria	***Inclusion Criteria:*** Male and female aged ≥18 years. Patient has a diagnosis of ADPKD between CKD Stages 1–3, and is deemed by their treating physician to likely have rapidly progressing disease. Patient has a life expectancy greater than 18 months at time of enrolment. Patient is able and willing to give informed consent, if required according to local regulations. Patient is fluent in local language. ***Exclusion Criteria:*** Patient is currently participating in or has in the last 12 months participated in an interventional clinical trial. Presence of any condition/circumstance which in the opinion of the investigator could significantly limit the complete follow up of the patient. Inability of the patient to complete PROs remotely.
Study type	Observational
Date of first enrolment	October 2016
Target sample size	486
Recruitment status	Active, not recruiting
Primary outcome(s)	Mean rate of change (%) in Physical Health Composite Scale (PCS) scores of the SF-12 from baseline to end of study, in the overall sample and per chronic kidney disease (CKD) stage.
Key secondary outcomes	Mean rate of change (%) in Mental Health Composite Scale (MCS) scores of the SF-12 from baseline to end of study, in the overall sample and per CKD stage. Mean ADPKD-IS scores changes from baseline to end of study, in the overall sample and per CKD stage (physical, emotional and fatigue domain scores will be reported and analysed). Mean TSQM-9 score changes from baseline to end of study, in the overall sample and per CKD stage (effectiveness, convenience and global satisfaction domain scores will be reported and analysed). Mean ADPKD-UIS score changes from baseline to end of study, in the overall sample and per CKD stage (frequency, urgency and nocturia domain scores will be reported and analysed). Mean ADPKD-PDS score change from baseline to end of study, in the overall sample and per CKD stage (dull kidney pain, sharp kidney pain and fullness/discomfort domain scores will be reported and analysed) Overall odds ratio of discrete-choice experiment (DCE) for patient preference to the addition of a disease modifying treatment versus no change to local Standard of Care (SoC) from baseline to end of study, in the overall sample and per CKD stage

## Background

Autosomal dominant polycystic kidney disease (ADPKD) is the most common inherited renal disease, affecting 3.29/10,000 people in Europe [1, 2]. ADPKD is caused by genetic mutations in one of two genes: polycystin 1 (PKD1) or polycystin 2 (PKD2), with approximately 10% of cases caused by an apparent de novo mutation [3]. The disease is characterized by the progressive increase in the number and size of bilateral renal cysts, causing hypertension, kidney pain and eventually kidney failure [4–6]. Symptoms of ADPKD can range from mild to severe, and worsen as disease progresses. Early symptoms can include: abdominal pain, high blood pressure, hematuria, increased vulnerability to urinary tract infections, nephrolithiasis, and urine concentrating defects [4, 7]. ADPKD is a leading cause of end stage renal disease (ESRD); by the age of 60 approximately 50% of ADPKD patients will progress to ESRD and will require either dialysis or a kidney transplant. ADPKD accounts for 5–10% of all ESRD patients [8].

Until recently, all treatments targeted the signs and symptoms of ADPKD, such as high blood pressure and pain, as a patient progressed to ESRD [9]. Tolvaptan, a vasopressin V2 receptor antagonist, is the first licensed ADPKD treatment shown to slow the progression of cyst development and renal insufficiency [10]. Tolvaptan promotes aquaresis and fluid loss, reducing the amount of fluid stored in the kidneys. Additionally, it reduces cyclic adenosine monophosphate (cAMP) levels, reducing the rate of kidney cell cyst proliferation [11]. Treatment with tolvaptan during early-stage chronic kidney disease (CKD) has been shown to slow total kidney volume growth and glomerular filtration rate (GFR) decline [10]. Based on clinical trial data, long-term treatment models indicate tolvaptan may delay ESRD by up to 6.5 years [12]. However, tolvaptan treatment can lead to hepatotoxicity and higher doses are not well tolerated due to a range of side effects, including aquaresis and polydipsia. In order to limit the impact of side effects, a large number of patients take a maximum tolerated dose, rather than the highest dose available, however the effect of tolvaptan on patient quality of life (QoL) has not yet been investigated [13, 14].

There is limited evidence to suggest that the QoL of patients with ADPKD is significantly lower than that of the general population. For example, a study in Japan found ADPKD patients scored significantly lower than the general population on physical, mental and social component summary scores of the health-related QoL (HRQoL) Short Form-36 (SF-36) questionnaire [2]. Previous research on HRQoL has mainly focused on the later stages of ADPKD (e.g. stages 4–5) and available data are derived from monocentric, cross-sectional studies conducted prior to the availability of tolvaptan [2]. A small number of studies have investigated QoL in early-stage ADPKD (CKD stages 1–3) finding that, while QoL is higher in early stages of the diseases than during the later stages, early-stage ADPKD has significant physical and emotional impact on patients [15, 16]. However, these studies used generic measures of HRQoL, rather than questionnaires specifically designed to assess the disease-specific effects ADPKD has on patients’ HRQoL. Thus, these findings may not present an accurate picture of the burden of the disease.

The ACQUIRE study is a multi-center, prospective, observational study investigating the real-world impact of ADPKD on patients at the early stages of the disease who have shown indications of rapidly progressing kidney dysfunction. This study aims to use ADPKD disease-specific measures to assess patients’ HRQoL in the early disease stages and as disease progresses. These findings may then be used to develop prognostic markers and treatment response prediction models. This study also aims to measure patient satisfaction and treatment preference using a Discrete Choice Experiment (DCE).

## Methods

### Study design

The ACQUIRE study is a prospective, observational study aiming to measure HRQoL, treatment preference and satisfaction and other patient reported outcomes (PROs) of ADPKD patients in Europe (Fig. 1). Data are prospectively collected at clinics, from medical notes and via PRO instruments for each patient at Baseline, Month 1, Month 3, and subsequently at 3-month intervals up to and including the final assessment (18 months maximum follow-up time). All data collection is expected to finish by the end of October 2019. Patients have been recruited from seven European countries: Austria, Belgium, France, Germany, Spain, Switzerland and the United Kingdom (UK).

**Fig. 1 Fig1:**
[figure not shown]
Study Design. ADPKD: autosomal dominant polycystic kidney disease; ADPKD-IS: ADPKD Impact Scale; ADKPD-PDS: ADPKD-Pain and Discomfort Scale; ADPKD-UIS: ADPKD-Urinary Impact Scale; CKD: chronic kidney disease; DCE: discrete choice experiment; SF-12: 12-item Short Form Health Survey; TSQM-9: Abbreviated Treatment Satisfaction Questionnaire for Medication

### Patient inclusion and exclusion criteria

Adult patients (≥18 years) with ADPKD in CKD stages 1–3, with evidence of rapidly progressing disease, and a life expectancy of longer than 18 months at the time of enrolment, were recruited to this study. These inclusion criteria are in line with the criteria for tolvaptan use in Europe [17]. The classification of rapid progression was left to the discretion of the doctor. European experts have proposed four ways to identify patients with evidence or risk of rapid ADPKD progression: [i] GFR slope, [ii] kidney growth rate, [iii] predictive model based on renal volume or renal length, or [iv] predictive model based on genetics [18]. All respondents were fluent in the local languages and were able and willing to give informed consent.

Individuals were excluded from the study if they were currently participating in, or had in the last 12 months participated in, an interventional clinical trial. Additional exclusion criteria included the presence of any condition/circumstance that, in the opinion of the investigator, could limit a complete 18-month study follow-up and prevent patients from completing the PRO questionnaires remotely. Based on a previous large study on a similar population, it was expected that the number of patients in each CKD stage would be approximately equal, so no restriction based on the number of patients at each early CKD stage was imposed during the recruitment stages (OVERTURE Study, NCT01430494) [19].

### Key study outcomes

The primary objective of this study is to describe the HRQoL of adult ADPKD patients in CKD stages 1–3 with rapidly progressing disease, overall and per CKD stage.

Secondary objectives of the study are to describe patient demographics, treatment satisfaction, the burden of aquaresis, and real-world ADKPD treatment patterns of adult ADPKD patients in CKD stages 1–3 with rapidly progressing disease, overall and per CKD stage.

This study also aims to investigate a range of exploratory outcomes. Specifically, change in patient reported pain scores from baseline (mean changes in dull kidney pain, sharp kidney pain and fullness/discomfort scores from the ADPKD Pain and Discomfort Scale [ADPKD-PDS]). The DCE will explore patient preferences for adding a disease modifying treatment versus no change to local standard of care, with the analysis exploring the relationships between treatment attributes and overall treatment preference. In addition, any relationship between DCE attribute preferences and persistence to ADPKD treatments will be investigated. Finally, exploration of possible relationships between variables of interest that could predict PRO instrument scores and other outcomes like persistence to ADPKD treatments may be carried out using Structural Equational Modelling (SEM). If SEM analyses are completed, the variables will be selected based on patient characteristics and potential differences in these between patient subgroups.

The primary endpoint assessed to measure HRQoL is the physical component score (PCS) of the 12-item Short Form Health Survey (SF-12) HRQoL questionnaire. The secondary endpoints include the mental component score (MCS) of the SF-12, the TSQM-9 and the disease-specific ADPKD-IS and ADPK-UIS. For both primary and secondary endpoints the outcome values and change from baseline values at each assessment, as well as the percentage change (%) from baseline to end of study measurements are recorded. These data will be presented for the overall sample, and for each CKD stage.

### Study procedures and measurements

Data are collected prospectively during clinic visits, from medical notes and from electronic questionnaires via a web-based data capture system that patients complete remotely. As this is an observational (real-world) study, patients are not required to attend additional clinic appointments; all data are collected during routine clinic visits.

At study baseline, patient demographics, medical history and current medication (both ADPKD-related and concomitant) are recorded. Additionally, medical outcomes (including patient reported adverse events), medication, and some PROs are collected at baseline and mid-study assessments at Month 1, Month 3 and then at 3-month intervals up to and including 18 months (Fig. 1). These PROs include HRQoL (measured by the SF-12 and ADPKD Impact Scale [ADPKD-IS]), treatment satisfaction (measured by the abbreviated Treatment Satisfaction Questionnaire for Medication [TSQM-9]), burden of aquaresis on patients (the ADPKD-Urinary Impact Scale [ADPKD-UIS]), and pain (the ADPKD-Pain and Discomfort Scale [ADPKD-PDS]). Patient treatment preferences (measured by DCE) are collected at baseline and during the final study visit. An overview of each questionnaire is provided below.

#### Patient questionnaires

General and disease-specific questionnaires are used to capture the patients’ assessment of their HRQoL, both broadly and with reference to specific symptoms and challenges faced when living with ADPKD. Questionnaires are completed remotely to allow flexibility and to ensure the information collected is reflective of real-world patients’ experience. Reminders to complete the questionnaire are sent via email at each timepoint to maximize questionnaire completion.

The SF-12 is a validated short questionnaire capturing the patient’s assessment of their functional health and well-being [20]. It has been developed as a shorter alternative to the SF-36 and covers 8 domains of HRQoL: physical functioning, role-physical, bodily pain, general health, vitality, social functioning, role-emotional, and mental health [21]. This study uses the SF-12 version 2 (4-week recall). The questionnaire is weighted and summed to provide easily interpretable scales of physical and mental health (PCS and MCS, respectively). Each scale is computed using scores from the 12 questions and scores range from 0 to 100, where 0 indicates the lowest level of HRQoL.

The TSQM-9 is a validated measure of patient satisfaction with medication and includes 3 domains: effectiveness, convenience, and global satisfaction [22]. It is based on the Treatment Satisfaction Questionnaire for Medication (TSQM) Version 1.4 and includes 9 of the 14 questions from this longer questionnaire (the TSQM-9 does not include questions about the side effects of medication) [23]. Similar to the SF-12 scales, the TSQM-9 domains are scored from 0 to 100, with higher scores representing greater satisfaction.

The ADPKD-IS measures the impact of ADPKD on a patient’s HRQoL using 3 domains: physical, emotional, and fatigue.^13, 14^ Each domain is measured by summing the score for each item in the domain and dividing the total number by the number of items in that domain. Each domain score is measured on a scale of 1–5, from 1, not difficult/bothered at all, to 5, extremely difficult/bothered, with a recall period of 14 days.

The ADPKD-UIS captures the burden of urinary concerns in ADPKD using 11 items that assess 3 domains: daytime urinary frequency, daytime urinary urgency, and nocturia [24]. ADPKD-UIS measures each domain by summing the score for each item in the domain and dividing it by the number of items in that domain. Each domain score is measured on a scale of 1–5 where 1 is not difficult/bothered and 5 is very difficult/bothered. The questionnaire has a recall period of 7 days.

Finally, the ADPKD-PDS measures the impact of three types of ADPKD-related pain: dull kidney pain, sharp kidney pain, and fullness/discomfort [25]. Each domain is measured on a 5-point scale, where 1 is no pain/discomfort and 5 is extreme pain/discomfort, with a recall period of 7 days.

#### DCE study

During the first and last study visits, a DCE questionnaire is administered to determine how highly patients value specific attributes of hypothetical alternative treatment options. A DCE is a health economic methodology used to explore the relative importance of each treatment attribute, helping to inform future treatment decisions [26]. DCE studies are used to quantify patient preferences for specific treatment attributes, and to investigate the role each treatment attribute plays in determining patient’s overall preference for a treatment [27]. Patients are offered a choice of hypothetical alternative treatments that are defined by different and varying attributes. Patients are asked to compare these hypothetical treatments and choose which they prefer. The analysis of patient responses across a number of different discrete treatment choices allows individual attributes to be ranked in order of patient preference.

The DCE used in this study was developed to measure patient-perceived relative importance of different treatment attributes (aquaresis, time to kidney failure, risk of serious and permanent liver damage, additional doctor/clinic visits, tablet number and routine). Patients are asked to assigned each attribute to one of 3 levels ranging from equal to the effects of local standard of care (e.g. ‘no additional urination or increased thirst’) to very different from the effects of local standard of care (e.g. ‘you have to go to the toilet and have to drink three times as much’) (Fig. 2). The orthogonal design (where the occurrence and level of each attribute is unrelated to any other attribute) of the DCE allows the assessment of the role and importance of each attribute in determining treatment preference from patient responses. The outcome is expressed as an odds ratio. Cognitive debriefing interviews and a steering committee of experts were used to validate the DCE study design, and a pilot test of the study was performed in a small number of patients (*n* = 5), which demonstrated that the study was internally and externally consistent [28].

**Fig. 2 Fig2:**
[figure not shown]
Example DCE Question. ADPKD: autosomal dominant polycystic kidney disease; ESRD: end stage renal disease

### Statistical analysis

#### Sample size calculation

This is a descriptive, observational study without requirement to power the sample for statistical inference. However, the statistical power for measurement accuracy (i.e. changes of the physical health scale measured by SF-12 from baseline) has been carried out for sample size estimation. This was based on observed variation of the physical health scale in the SF-12 questionnaire in a previous study on a similar population (OVERTURE Study, NCT01430494) [19]. The primary endpoint of the ACQUIRE study is the percentage change between baseline and throughout the observational points in the PCS of the SF-12 questionnaire. Assuming a loss of follow-up of 40% (similar to the 37% rate in the first 18 months of the OVERTURE study), a sample size of 162 patients per CKD stage (486 patients total) allows the detection of an average change of 1.4 points in PCS from baseline to the end of the study with 95% confidence interval (assuming a similar standard deviation [SD] to the OVERTURE study [SD = 7.0]). A 2.5 point change is considered clinically relevant and important in this disease area, so this sample size is sensitive enough to detect clinically relevant changes (1.4 point and above) in patients’ HRQoL [29]. Therefore, the target sample size has been defined as 480 patients. It is expected that approximately 20–25 centers, with 15–30 patients per center will provide the representative sample required in the study.

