#### Statistical analysis of data

Data will be summarized using summary statistics. For continuous data the number of observations, numbers of missing data points, the mean, standard deviation, minimum, first quartile, median, third quartile and maximum will be reported. Counts and percentages will be presented for categorical data. Real-world treatment patterns for ADPKD patients, both overall and CKD stage, will be reported in this way.

The primary efficacy analysis is the change in PCS on the SF-12 questionnaire. For each visit the PCS will be summarized. The absolute values, change from baseline values and mean percentage change from baseline will be reported overall and for each CKD stage. The percentage change will be calculated as follows:
$$ Percentage\ change=\frac{100\times \left( score\  at\  end\  of\ study- score\  at\  baseline\right)}{score\  at\  baseline} $$

The secondary efficacy analysis is the change in the MCS on the SF-12 questionnaire. For each visit, overall and for each CKD stage the MCS will be summarized by the absolute values, change from baseline values and mean percentage change from baseline. The percentage change will be calculated as described above.

The absolute values, change from baseline values and mean percentage change from baseline will be reported for each CKD stage and overall for each questionnaire, at each timepoint. As an exploratory outcome, SEM analysis may be used to identify relationships between variables that could predict PRO scores and other outcomes, such as persistence, the act of continuing treatment for the prescribed duration [30]. Any hypotheses will be developed prior to the analysis of the final data set, but will be based on patient characteristics as baseline. Until baseline results are available, factors that may differ between patient subgroups and any resulting SEM hypotheses cannot be fully defined.

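### The primary endpoint is a mean of individual percentage changes in PCS, but the study is sized and judged in points, and that mean is positive even when the average change is zero

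*Protocol article*

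**What the plan says.** The primary outcome in the WHO registration data set table is "Mean rate of change (%) in Physical Health Composite Scale (PCS) scores of the SF-12 from baseline to end of study", overall and per CKD stage. The sample size section says "The primary endpoint of the ACQUIRE study is the percentage change between baseline and throughout the observational points in the PCS". The section on statistical analysis of data says "The primary efficacy analysis is the change in PCS on the SF-12 questionnaire", without the word percentage. It then gives the formula ("The percentage change will be calculated as follows"): 100 times the difference between the end-of-study and baseline scores, divided by the baseline score.

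The same section extends the measure: "mean percentage change from baseline will be reported for each CKD stage and overall for each questionnaire, at each timepoint". The disease-specific scales start at 1, not 0. For the ADPKD-IS, "Each domain score is measured on a scale of 1–5, from 1, not difficult/bothered at all, to 5, extremely difficult/bothered"; for the ADPKD-UIS, "Each domain score is measured on a scale of 1–5 where 1 is not difficult/bothered and 5 is very difficult/bothered". The ADPKD-PDS is also a 5-point scale on which 1 is no pain. TSQM-9 domains run from 0 to 100.

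The sample size is argued wholly in points: 162 patients per stage (486 in total), 40% loss to follow-up, SD 7.0, a detectable mean change of 1.4 points, and 2.5 points as clinically relevant.

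**The concern.** There are two separate problems.

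- **Scale.** The study is sized, and its result is to be judged, in points, but the named endpoint is a percentage. Converting one to the other needs a baseline mean and an SD of percentage change. The article gives neither.
- **Estimator.** Each patient's own baseline, measured with error, is the denominator. A patient whose baseline is low by chance tends to rise and is divided by a small number. One whose baseline is high by chance tends to fall and is divided by a large number. The average ratio is therefore pushed upwards when nothing has changed on average. For PCS that looks like improvement. For the 1–5 scales, where higher is worse, it looks like deterioration.

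In a descriptive study the headline estimate is the result, so its definition matters even without a hypothesis test.

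**Working it through.** **1. The plan's own figure.** Inputs from the sample size section: SD 7.0, 1.4 points, 95% confidence, 40% loss.

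- n = (1.96 × 7.0 / 1.4)² = 96.04, so 97 evaluable.
- 97 / 0.6 = 161.7, so 162 enrolled per stage; 3 × 162 = 486.
- Half-width with 97 evaluable: 1.96 × 7.0 / √97 = 1.39 points.

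The figure is reproduced, but only on the point scale.

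**2. Translation to percent** (baseline mean PCS of 40, 45 or 50 is an assumption).

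- 1.4 points = 3.5%, 3.1%, 2.8%.
- 2.5 points = 6.25%, 5.6%, 5.0%.

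Both targets move with a mean that the article does not state.

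**3. Artefact at zero mean change.** With equal mean μ and SD at both times and correlation r, a second-order expansion gives

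E[(Y − X)/X] ≈ (1 − r) × SD² / μ² = SD_change² / (2μ²).

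The article does not say whether 7.0 is the SD of the score or of its change, so both readings are shown.

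- 7.0 as SD of change: 24.5/μ² = 1.53%, 1.21%, 0.98% at μ = 40, 45, 50.
- 7.0 as cross-sectional SD, r = 0.7 assumed: 14.7/μ² = 0.92%, 0.73%, 0.59%.

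Simulation (2,000,000 pairs, mean point change zero; score SD of 7 with r = 0.5, or 10 with r = 0.755, for the first reading) gave:

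| Reading of 7.0 | μ | Mean % change | In points | Half-width, n = 97 | Half-width, n = 291 |
|---|---|---|---|---|---|
| SD of change | 40 | 1.71–1.83 | 0.68–0.73 | 3.76–3.94 | 2.17–2.27 |
| SD of change | 45 | 1.29–1.43 | 0.58–0.64 | 3.28–3.45 | 1.89–1.99 |
| SD of change | 50 | 1.05–1.12 | 0.52–0.56 | 2.92–3.03 | 1.68–1.75 |
| SD of score, r = 0.7 | 40 | 1.03 | 0.41 | 2.88 | 1.66 |
| SD of score, r = 0.7 | 45 | 0.80 | 0.36 | 2.52 | 1.46 |
| SD of score, r = 0.7 | 50 | 0.62 | 0.31 | 2.25 | 1.30 |

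Half-widths are in percent; 291 is 486 × 0.6. A second simulation put the top of the first reading at 1.9%. A spread wider than the plan assumes (score SD 10, r = 0.5) would give 2.3% to 3.8%.

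Two patients show the mechanism. A change from 40 to 50 is +25% and from 50 to 40 is −20%. The mean is +2.5%, with a mean change of 0 points.

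**4. The 1–5 scales.** A change from 1 to 2 is +100% and from 2 to 1 is −50%, so the mean is +25% with no mean change. The origin is arbitrary: if the scale were recoded 0–4, a step from 2 to 3 (+50%) would become 1 to 2 (+100%). Two sets of assumed inputs gave:

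- means 1.6–2.5, SD 0.7–0.9, r 0.6–0.8: +1.9% to +4.2%;
- means 1.5–2.0, SD 0.7–0.9, r 0.6–0.7: +4.5% to +7.1%.

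The shape of the distribution matters too. At mean 2.0, SD 0.8, r = 0.6 the expansion gives 0.4 × 0.64 / 4 = 6.4%, while a skewed simulation gives 4.2%.

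**5. TSQM-9.** With assumed means of 60–65, SD 20 and r 0.5–0.6, the expansion gives 3.8% (0.4 × 400 / 65²) to 5.6% (0.5 × 400 / 60²), and simulation gives about 6% to 10%. In one scenario, moving the lower cut-off for scores from 10 to 0.01 changed the result from 7.8% to 12.9%. The size is set by the tail near zero, on which the article is silent.

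**The case against.** The strongest defence is that the useful number is already planned. The sections on key study outcomes and on statistical analysis both promise absolute values and change from baseline at each assessment, overall and per stage, beside the percentage. A reader could infer that the result cannot be compared with the 2.5-point threshold. That is true of the percentage line only, not of the planned output. The study is descriptive, and its limitations section disclaims formal hypotheses and firm conclusions, so no test or success criterion hangs on the percentage. This stands, and it lowers the severity.

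Other strong readings also go too far:

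- **Per-stage PCS results are materially distorted.** The artefact lies inside the per-stage half-width in every row of the table. Moving the assumed mean from 50 to 40 changes it by only about 0.4 to 0.7 percentage points. The article gives no stage-specific means or spreads that would support more.
- **The article defines three conflicting primary endpoints.** The key study outcomes section largely reconciles them: values and changes at each assessment, and the percentage from baseline to end of study. What remains is the loose phrase in the sample size section about all observation points, and the missing word percentage in the analysis section.
- **An undefined percentage at a TSQM-9 baseline of 0 is an omission.** It is possible on that scale, but a handling rule is commonly left to the SAP, which is not shown.

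A percentage change of group means would also escape the bias. The article does not say that, and a score-level formula followed by a mean percentage change reads naturally as an average of individual percentages.

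**Conclusion.** The point holds as a should-fix. That the named endpoint and the sample size are on different scales follows from the text without any assumption. The arithmetic behind 162 per stage is correct, and a reader should not infer otherwise.

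The upward artefact is a property of the formula; its size rests on assumptions. For PCS it is about +0.6% to +1.0% if 7.0 is the cross-sectional SD (r = 0.7), or +1.0% to +1.9% if it is the SD of change, with a baseline mean of 40–50. That is roughly 0.3 to 0.75 points, or 12% to 30% of the 2.5-point threshold. It sits inside the per-stage 95% half-width (about 2.3% to 4.0%) but takes a larger share of the overall one (about 1.3% to 2.3%).

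For the 1–5 scales, +2% to +7% false worsening is illustrative; the lack of a meaningful origin is the firmer objection. No reliable size can be given for TSQM-9.

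**What to change.** 1. Name the mean change in PCS points from baseline to end of study, overall and per CKD stage with a 95% CI, as the primary summary. Use the same wording in the registration data set table, the sample size section and the statistical analysis section.
2. Keep the registered percentage for the SF-12 scores as a supplementary line, computed as 100 × (mean change) / (mean baseline).
3. Drop percentage change for ADPKD-IS, ADPKD-UIS, ADPKD-PDS and TSQM-9. The registration table already lists their outcomes as score changes.

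The sample size stands unchanged: 97 evaluable and 162 enrolled per stage, with a half-width of 1.39 points. No new data or patients are needed, since point changes are already computed at each visit. The cost is more than an edit of wording. The percentage is the registered primary outcome and the table gives recruitment as closed, so the change needs a documented amendment to the protocol and the registry entry.
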